## Abstract

**Background:**

Premature menopause is a major concern of younger women undergoing adjuvant therapy for breast cancer. Hormone replacement therapy is contraindicated in women with a history of breast cancer. Non-hormonal medications show a range of bothersome side-effects. There is growing evidence that cognitive behavioral therapy (CBT) and physical exercise can have a positive impact on symptoms in naturally occurring menopause. The objective of this study is to investigate the efficacy of these interventions among women with breast cancer experiencing treatment-induced menopause.

**Methods/design:**

In a randomized, controlled, multicenter trial, we are evaluating the effectiveness of CBT/relaxation, of physical exercise and of these two program elements combined, in reducing menopausal symptoms, improving sexual functioning, reducing emotional distress, and in improving the health-related quality of life of younger breast cancer patients who experience treatment-induced menopause. 325 breast cancer patients (aged < 50) are being recruited from hospitals in the Amsterdam region, and randomly allocated to one of the three treatment groups or a 'waiting list' control group. Self-administered questionnaires are completed by the patients at baseline, and at 12 weeks (T1) and 6 months (T2) post-study entry. Upon completion of the study, women assigned to the control group will be given the choice of undergoing either the CBT or physical exercise program.

**Discussion:**

Cognitive behavioral therapy and physical exercise are potentially useful treatments among women with breast cancer undergoing treatment-induced, premature menopause. For these patients, hormonal and non-hormonal therapies are contraindicated or have a range of bothersome side-effects. Hence, research into these interventions is needed, before dissemination and implementation in the current health care system can take place.

**Trial registration:**

The study is registered at the Netherlands Trial Register (NTR1165) and ClinicalTrials.gov (NCT00582244).

## Background

Breast cancer is the most common cancer among women in the Netherlands, with an incidence of 71 per 100.000 person years, and a lifetime risk of 10%. [1] Nearly 25% of all women with breast cancer are premenopausal at the time of diagnosis. [2] Ovarian damage is the most significant long-term sequela of chemotherapy and/or endocrine treatment in premenopausal women. [3,4] It can lead to an earlier onset of menopause, with age and duration of treatment being its strongest predictors. [5] Premature menopause is a major concern of younger women undergoing adjuvant therapy for breast cancer [6], as effective and safe treatment options are not currently available.

### Premature menopause and menopausal symptoms

Primary menopausal symptoms include hot flushes, night sweats, vaginal dryness, decreased libido, dysuria and urinary incontinence. Secondary symptoms include insomnia due to night sweats, dyspareunia because of vaginal dryness, weight gain, and psychological distress. [3,7,8] Previous studies have indicated that breast cancer patients are more likely to experience menopausal symptoms than age-matched healthy controls, [9,10] and that especially younger breast cancer patients are affected by vasomotor and dystrophic symptoms. [7] Menopausal symptoms are an important source of morbidity [11] and discomfort [7,8] in patients with breast cancer and they may adversely affect women's sexual functioning, body image, and overall health-related quality of life. [6,9,12,13]

Among menopausal symptoms, hot flushes are considered to be the most disruptive, with prevalence rates between 63% and 80% in breast cancer patients. [8,14-17] Dysfunction of the thermoregulatory center in the hypothalamus due to (natural or treatment-induced) changes in estrogen levels has been postulated to be the cause of hot flushes. [18] As stress, spicy food and alcohol intake potentially affect the levels of serotonin, they may also increase the frequency and intensity of hot flushes. [19,20]

### Treatments for menopausal symptoms

Hormonal replacement therapy (HRT) is highly effective in alleviating vasomotor symptoms associated with menopause. [21] However, HRT is contraindicated in women with a history of breast cancer. [22] Some of the non-hormonal medications, e.g. clonidine and selective serotonin receptor inhibitors, have been shown to be moderately effective in reducing vasomotor symptoms associated with menopause. [23] However, they have a range of bothersome side-effects, such as nausea, dizziness and dry mouth. [24-27]

There is growing evidence that cognitive behavioral therapy and physical exercise can have a positive impact on symptoms in naturally occurring menopause. [28-30] Cognitive behavioral therapy (CBT) focuses on the relationships between thoughts, feelings and behavior, and is aimed primarily at stress reduction. CBT includes the following components: information about symptoms, monitoring and modifying precipitants, relaxation and stress management, cognitive restructuring of unhelpful assumptions and automatic thoughts, and encouraging helpful behavioral strategies. [28] A four session CBT including relaxation was found to be as beneficial in the reduction of vasomotor symptoms as HRT in a study of women undergoing natural menopause, and more effective than HRT in improving mood. [31]

Several studies have reported that relaxation therapy can effectively reduce hot flushes in naturally menopausal women, which may be explained by the reduction of sympathetic nervous system activity. [29,32,33] Significant associations have been observed between ratings of stress and reports of hot flushes, [19,20] suggesting that modification of precipitants of hot flushes and stress management may decrease the frequency and severity of hot flushes.

To our knowledge, only two studies have investigated the efficacy of behavioral interventions for the treatment of menopausal symptoms among women with breast cancer. In a randomized, prospective trial, Ganz et al. [34] found a significant, positive effect of a treatment package including counseling, pharmacological and behavioral interventions on menopausal symptoms and sexual functioning among women with a history of breast cancer. In a small randomised study (n = 16), relaxation training yielded a trend toward lower levels of hot flushes and night sweats, and a significant positive effect on psychological distress as compared to a control condition. [35]

A number of studies have generated results indicative of a beneficial effect of physical exercise on hot flushes occurring in naturally menopausal women. Two large population-based, cross-sectional studies carried out among Swedish women [36,37] indicated that regular vigorous exercise at least 3 hours per week is associated with a significantly lower risk of hot flushes. Only 5% of highly active women experienced severe hot flushes as compared to 15% of women who had little or no weekly exercise. It has been hypothesized that the positive effect of exercise on vasomotor symptoms may be due to elevated levels of endorphins that regulate central thermoregulation. [36,37] The findings of these observational investigations were further supported by two randomized studies conducted in Sweden and Japan [30,38] showing that a physical exercise program of at least 12 weeks had a significant positive effect on climacteric symptoms and health-related quality of life. However, one randomized study [39] has reported increased rates of hot flushes among obese, sedentary, postmenopausal women participating in an exercise program. This latter finding may be related to weight loss and decreased fat content leading to a decline in estrogen levels. [40]

Although cognitive behavioral therapy and physical exercise have been shown to have favorable effects in women undergoing natural menopause, these interventions have not yet been investigated in the context of menopausal symptoms experienced by breast cancer patients undergoing treatment-induced menopause.

### Current study

The present study is systematically evaluating the effectiveness of CBT/relaxation, of physical exercise and of these two program elements combined, in reducing menopausal symptoms, improving sexual functioning, reducing emotional distress, and in improving the health-related quality of life of younger breast cancer patients who experience treatment-induced menopause. In a randomized, controlled, multicenter trial, we are comparing CBT (A), physical exercise (B) and the combination of both interventions (AB) to a 'waiting list' control group.

We hypothesize that women in the CBT group, the physical exercise group or the combined group will report significantly greater reduction in overall levels of menopausal symptoms than patients in the usual care, waiting list control group. Furthermore, we hypothesize that women participating in the combined intervention will report significantly greater reduction in overall levels of menopausal symptoms than those participating in the CBT only or in the exercise only groups. Due to different mechanisms of action, we expect that the combined modalities will be more effective than either modality alone. CBT is expected to lead to significant reductions in menopausal symptoms via cognitive restructuring and stress management, while physical exercise is expected to impact primarily on metabolism of neurotransmitters responsible for thermoregulation. Finally, we hypothesize that women exposed to the interventions (groups A, B and AB) will report significantly more improvement in sexual functioning, body- and self-image, psychological distress, and generic health-related quality of life than those in the control group.

If demonstrated to be effective, the availability of such a structured supportive intervention program will be a welcome addition to standard medical treatment offered to breast cancer patients with treatment-induced menopause. It is anticipated that such a program will have direct benefit in terms of symptom relief and the improvement of patients' health related quality of life.

## Methods and design

Using a 2 × 2 full-factorial design patients are randomly allocated to one of the four following conditions: CBT, physical exercise, the combination of both interventions or a 'waiting list' control group. The design will allow for testing of the main effect of CBT, the main effect of physical exercise, and the additive or interactive effects of CBT and exercise on menopausal symptoms, the primary outcome measure. Secondary outcomes will include sexual functioning, urinary symptoms, body image and self-image, psychological distress and HRQL. The design of the study and the anticipated flow of the participants are graphically shown in Figure 1. The institutional review boards of all participating hospitals have approved the study. The study is registered at the Netherlands Trial Register (NTR1165) and ClinicalTrials.gov (NCT00582244).

**Figure 1 F1:**
[figure not shown]
**Study flow diagram**.

### Study sample

The study sample will be composed of 325 women, younger than 50 years of age, with histologically confirmed primary breast cancer (stages: T1 – T4, N0 – N1 and M0). All women will have been premenopausal at the time of diagnosis, have completed adjuvant chemotherapy a minimum of 4 months and a maximum of 5 years prior to study entry, and will currently be disease-free. Hormonal therapy can still be ongoing. Potentially eligible women are screened for the presence of at least one of the following 3 menopausal symptoms during the previous week: hot flushes, sweating and/or vaginal dryness. Women are excluded from the study if they lack basic proficiency in Dutch, if they have serious cognitive or psychiatric problems, or serious physical comorbidity that would preclude them from participating in a physical exercise program. Since physical exercise may be contraindicated as a treatment for hot flushes in obese women, [39] patients with a BMI ? 30 are excluded from the study. Patients participating in concurrent studies or rehabilitation programs containing comparable psychosocial interventions are also excluded.

### Sample size

The FACT-ES scale, assessing endocrine symptoms [41] is the primary outcome on which sample size calculations are based. Specifically, mean group differences in the FACT-ES scores at 12 weeks and 6 months follow-up, controlling for baseline value, will serve as the primary endpoint of the study. With a total sample of 260 women (65 per group), and under the assumption of no interaction, the study will have 90% power to detect an effect size of 0.4 for the main effects of CBT (n = 130) and physical exercise (n = 130), with the p-value set at 0.05. If the combined effects of CBT and physical exercise are cumulative, or if the effect of CBT varies as a function of exposure to exercise or vice versa, (i.e. there is a significant interaction between CBT and exercise), this number of patients will allow testing each of the 4 cells in the factorial design (group A, B, AB and control group) separately with 80% power to detect an effect size of 0.5, again with p-value set at 0.05. [42]

We will recruit 325 women into the study, to allow for an attrition rate of approximately 20% (i.e. women who discontinue participation in the study entirely, including failure to complete all follow-up questionnaires; those women who discontinue participation in one of the groups but complete the follow-up assessments will be included in the analysis). Thus, 260 women will be available for the primary intention-to-treat analysis.

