### Recruitment and randomisation

The patients are recruited from hospitals in the Amsterdam region. Potentially eligible patients are identified through hospital registries, for the 5-years retrospective inclusion, and through treating physicians, for the 2-years prospective inclusion. They are sent a letter signed by their physician informing them of the study and, if initially interested, asking them to complete a brief questionnaire to screen for menopausal symptoms. If they have no further interest in the study, they are asked to complete a postcard indicating reasons for not participating. In case of no response to the questionnaire or the postcard, a reminder is sent two weeks after the first mailing.

Those women who meet criteria for study entry based on their questionnaire responses are contacted by telephone to provide additional information on the study and to confirm their eligibility. In addition, they receive an extensive baseline questionnaire and informed consent form by mail. Computerized randomization takes place after response to both this baseline assessment and the informed consent. Block randomisation is used to ensure that each intervention consists of equally sized groups. In view of the nature of the interventions, blinding of the participants and the researchers is not possible.

During the follow-up period, self-administered questionnaires are sent to the patients at 12 weeks (T1) and 6 months (T2) post-study entry. Upon completion of the study, women assigned to the control group will be given the choice of undergoing either the CBT or physical exercise program.

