### Statistical analyses

Analysis will first be performed to evaluate the comparability of the intervention and control groups at baseline in terms of sociodemographic and clinical characteristics. Student's t-test or appropriate non-parametric statistics will be used, depending on the level of measurement. If, despite the stratified randomization procedures, the groups are found not to be comparable on one or more background variables, those variables will be employed routinely as covariates in subsequent analyses.

Scores for the FACT-ES, the Hot Flush Rating Scale, the BFLUTS, the SAQ, the QLQ-BR23 body image scale, the HADS, and the SF-36 will be calculated according to published scoring algorithms. Between-group differences over time in mean scores will be tested using a two factor (group × time) multivariate analysis of variance with repeated measures on the time factor. Effect sizes will be calculated using standard statistical procedures. All analysis will, to as great an extent as possible, be conducted on an intention-to-treat basis. In addition, we will perform per-protocol analyses based on patients who complete the entire intervention. As indicated previously, the FACT-ES and the Hot Flush Rating Scale will be used as the primary study endpoints, and the remaining measures will be considered as secondary endpoints. For the analysis of these latter variables, appropriate statistical (p-value) adjustments will be made for multiple testing.

Supplementary analyses will be carried out in which data relating to compliance with the program elements is taken into account. Specifically, we will determine whether the level of compliance (based on attendance records, self-report data and, in the case of physical exercise, data stored in the heart rate monitor) is associated significantly with the changes over time in symptom relief, sexuality, body image, psychological distress, and health related quality of life.

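### The set labelled intention-to-treat is the women expected to complete follow-up, and the repeated-measures MANOVA in its standard form drops any woman missing one of the two primary assessments

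*Protocol article*

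**What the plan says.** All of this is in the protocol article.

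- **Sample size, planning figure.** The power statement rests on 260: "With a total sample of 260 women (65 per group), and under the assumption of no interaction". Recruitment is then raised: "We will recruit 325 women into the study, to allow for an attrition rate of approximately 20" per cent.
- **Sample size, who counts as lost.** Attrition covers "women who discontinue participation in the study entirely, including failure to complete all follow-up questionnaires". Women who leave an intervention are treated differently: "those women who discontinue participation in one of the groups but complete the follow-up assessments will be included in the analysis".
- **Sample size, the label.** "Thus, 260 women will be available for the primary intention-to-treat analysis".
- **Sample size, the endpoint.** The primary endpoint is the group difference in FACT-ES at both 12 weeks (T1) and 6 months (T2), adjusted for baseline.
- **Recruitment and randomisation.** "Computerized randomization takes place after response to both this baseline assessment and the informed consent".
- **Statistical analyses.** The stated model is a group-by-time MANOVA with repeated measures on time. The population statement is qualified: "All analysis will, to as great an extent as possible, be conducted on an intention-to-treat basis". A per-protocol analysis of women who finish the whole intervention is separate.
- **Compliance.** The investigators try hard to obtain a final assessment from women who stop the programme.

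**The concern.** Intention-to-treat means all randomised women, analysed as allocated. Randomisation follows the baseline questionnaire, so every woman lost to attrition has been allocated and has a baseline score. A set defined by who later returned questionnaires is selected on a post-randomisation event, and randomisation no longer guarantees that the groups compared are alike.

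The model adds a second loss. A repeated-measures MANOVA in its standard form needs a complete row for each woman. One who returned T1 but not T2 would drop out, although half of her primary endpoint was observed.

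Unequal loss is plausible here. Participants and researchers are not blinded, outcomes are self-reported, and the arms differ in burden: six weekly group sessions with homework and a booster, 2.5 to 3 hours of exercise a week for 12 weeks, both together, or waiting. A reader told that the result is intention-to-treat would assume a protection against selection that the stated analysis does not give.

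**Working it through.** **1. The protocol's own figures.** Inputs from Sample size: 325 recruited, about 20% attrition, 260 analysed, 130 per main-effect margin, 65 per cell, effect sizes 0.4 and 0.5, alpha 0.05 (sidedness is not stated; two-sided reproduces the figures).

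- 325 × (1 − 0.20) = 260, and 260 / 0.80 = 325. Expected loss is 325 − 260 = 65, and 65 / 325 = 20%.
- Power ≈ Φ(d × √(n/2) − 1.96).
  - Main effect: 0.4 × √(130/2) − 1.96 = 1.265, power 0.897 (stated 90%).
  - Cell: 0.5 × √(65/2) − 1.96 = 0.890, power 0.813 (stated 80%).

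The sample size arithmetic is sound. Raising recruitment to cover attrition is correct and is not the problem.

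**2. Who is in the 260.** The attrition wording can be read in two ways.

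| Reading | Women with only T1 or only T2 | Effect of the standard MANOVA |
|---|---|---|
| Missing *any* follow-up questionnaire counts as attrition | Among the 65 lost | 260 is the complete-case number; observed scores from women with partial follow-up are discarded |
| Returning *no* follow-up questionnaire counts as attrition | Among the 260 | They are dropped by the model, so fewer than 260 are analysed |

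Either way, the label and the model do not match an intention-to-treat analysis.

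**3. Possible bias (assumed values; the documents give none).** Suppose there is no true effect. Let a fraction p of an arm be lost, with the lost women scoring G standard deviations worse than those observed. If the whole arm averages zero, the observed women average p × G in the favourable direction. The spurious difference between two arms is (p₁ − p₀) × G.

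Take p = 0.30 in each active arm, p = 0.10 in control, and G = 0.3 to 0.5.

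- *One active arm against control:* (0.30 − 0.10) × 0.3 to 0.5 = 0.06 to 0.10 SD. Against the planned cell effect of 0.5, that is 12 to 20%.
- *Factorial main effect, the two cells of each margin weighted equally:* the CBT margin (CBT, combined) loses 30%. The no-CBT margin (exercise, control) loses (30 + 10)/2 = 20%. The bias is (0.30 − 0.20) × 0.3 to 0.5 = 0.03 to 0.05 SD. Against the planned 0.4, that is 7.5 to 12.5%. The exercise margin is the same by symmetry.
- *Equal loss, equal gap:* (0.20 − 0.20) × G = 0.

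This scenario implies an overall loss of (3 × 30 + 10)/4 = 25%, somewhat above the protocol's allowance.

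**4. Equal loss alone is not enough.** With 20% lost in every arm and an effect of 0.4 SD among women observed, the effect in all randomised women is 0.8 × 0.4 + 0.2 × (effect in those lost). It is 0.36, 0.32 or 0.28 SD if the effect in those lost is 0.2, 0 or −0.2 SD (assumed values).

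**The case against.** The strongest reply is that the 260 is a forecast of available data, not a rule that removes anyone. The 20% is an approximate recruitment allowance, and nothing instructs the analyst to discard 65 women. The commitment to intention-to-treat is explicit though qualified, outcomes are sought from women who stop the programme, those women stay in the analysis if they return questionnaires, and the per-protocol analysis is kept apart. The MANOVA text does not mention deletion, imputation beforehand is not ruled out, and a condensed article may leave missing-data detail to another document.

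Much of this stands. A reader might infer that the plan analyses only women who completed treatment, or that it orders one randomised woman in five to be thrown out. The documents support neither.

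A reader might also set the 0.06 to 0.10 SD bias against the planned 0.4. That mixes two comparisons: 0.4 is the factorial main effect, where the same assumptions give half as much.

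The reply does not remove the point. The article itself says who is counted in, names that set intention-to-treat and names a model. Together these describe a complete-case analysis under another label, which is a statement to correct and not merely detail left out. The qualification in Statistical analyses does not say how incomplete follow-up is handled.

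**Conclusion.** The point holds as a mislabelled analysis set combined with a model that, in its standard form, wastes partial follow-up. It should be corrected, but it does not undermine the design or the sample size.

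The firm figure is the planning one: about 65 of 325 women (20%) are expected to fall outside the set called intention-to-treat. If attrition means returning no questionnaire at all, the MANOVA would analyse fewer than 260.

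The documents establish a risk of attrition bias, not its size or direction. The ranges of 0.03 to 0.05 SD on a main effect and 0.06 to 0.10 SD on one active arm against control rest entirely on the assumed 30% and 10% losses and the assumed 0.3 to 0.5 SD gap.

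A reader might also infer that redefining the population lifts main-effect power from 90% to 95%. It does not: 0.95 is an upper bound that requires observed outcomes from all 325 women. A better model recovers partial follow-up, not outcomes that were never observed.

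**What to change.** 1. Define the primary population as all randomised women, analysed as allocated.
2. Replace the repeated-measures MANOVA with a likelihood-based mixed model for T1 and T2, with baseline as covariate, using every available score. This also matches the baseline-adjusted endpoint described under Sample size. It relies on scores being missing at random given the data in the model.
3. Relabel the 260 as the expected number with complete follow-up, and say whether attrition means missing any follow-up questionnaire or all of them.
4. Optionally, add a delta-adjusted sensitivity analysis, with the shift varied separately by arm, for women with no follow-up score. With baseline as covariate, the mixed model draws no information from them.

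The cost is analysis wording, a standard model and, if wanted, one sensitivity analysis. No extra patients or data are needed, and the sample size stays as it is.
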